#### Injury-Related Fear (Aim 2a)

Injury-related fear will be measured by the TSK-11. The TSK-11 is a valid and reliable questionnaire that consists of 11 items scored on a 4-point Likert scale, which evaluates fear of movement and reinjury [36]. The score ranges from 11 to 44, with higher scores representing higher injury-related fear. The TSK-11 has been utilized in patients with ACLR [42], low back [36], upper extremity [36,43], and lower extremity disabilities [4]. Participants will complete the TSK-11 during screening to determine eligibility for the study based on elevated injury-related fear (>17). For participants consented into the trial, they will complete the TSK-11 at preassessment (wk 1), weeks 2, 4, and 6 of the intervention/sham, and the postassessment (wk 8) (Table 1).

#### Jump-Landing Biomechanics (Aim 2b)

Jump-landing biomechanics will be assessed by measuring peak knee abduction moments and knee flexion excursion during a drop vertical jump task with a 3D motion capture system. Participants will complete 3 successful trials of a drop vertical-jump assessment to evaluate external knee abduction moments and knee flexion excursion [44]. Participants will be instructed to drop directly down off a 30-cm box with 1 foot on each force plate and immediately perform a maximum vertical jump. Twenty-nine retroreflective markers will be placed bilaterally on the first and fifth metatarsal heads, medial and lateral malleoli, calcaneus, tibia, medial and lateral epicondyles, thigh, grater trochanter, anterior superior iliac spine, acromioclavicular joint, sternum, and L4/L5, and a cluster of 3 markers will be placed over the sacrum [44]. Prior to biomechanical testing, a static standing trial will be completed to assess lower extremity lengths between proximal and distal joint centers. Height of the center of mass will be calculated from the mass and inertial properties of each segment.

The 3D kinematic data will be sampled at 120 Hz using a 10-camera Bonita motion capture system (Vicon Motion Systems Ltd) and low-pass filtered at 10 Hz (fourth-order recursive Butterworth). Ground reaction forces will be collected at 1200 Hz using 2 calibrated force plates (AMTI OR-6) fixed in the floor and low-pass filtered at 75 Hz (fourth-order recursive Butterworth). Peak knee abduction moment will be calculated within the first 100 ms after initial contact of the foot on the force plate (ie, when vertical ground reaction force rises above 20 N), as this is when most noncontact ACL injuries occur [45]. Knee flexion excursion will be calculated during the landing phase (time between ground contact and peak knee flexion angle [46]). Inverse dynamics will be used to calculate moments and will be normalized to body weight and height (BW×m) [46]. Data will be analyzed using MATLAB (The MathWorks Inc) and LabVIEW (National Instruments).

### Statistical Analysis

Descriptive statistics (means, SD, frequency, and ranges) will be calculated for recruitment, retention rates, adherence, and acceptability outcomes. A threshold of 75% or better will be used as the minimum threshold for acceptable recruitment, adherence, and retention outcomes. A threshold of 50% will represent moderate acceptability, and scores of 80% or better will be used to identify high acceptability [40].

Descriptive statistics will be calculated for participant demographics, TSK-11 scores, peak knee abduction moment, and knee flexion excursion. A 2×2 repeated measures ANOVA will be used to assess changes between the intervention and sham groups. Group and time will serve as our independent variables. The TSK-11 score, peak knee abduction moment, and knee flexion excursion will serve as our dependent variables. The results will be reported as means and mean differences, with 95% CIs, *F*-values (ratio of between-group variance to within-group variance), and *P* values. The significance level will be set at a corrected value of *P*<.02 to reflect multiple comparisons (0.05/3). We hypothesize that patients in the VRMM+NTR group will demonstrate lower injury-related fear, decreased external knee abduction moment, and increased knee flexion excursion when compared to the VR sham+NTR group. Hypotheses for each outcome will be tested independently. We believe that these statistical differences will be supported with moderate to strong effect sizes. Partial η^2^ effect sizes will be calculated to examine the magnitude of the Group × Time interaction. Effect sizes will be interpreted as small if between 0.01 and 0.08, medium if between 0.09 and 0.24, and large if >0.25 [47].

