## Methods

### Study Design

A double-blinded, 2-arm feasibility trial will be conducted to investigate a VRMM intervention. To address aim 1, recruitment, retention, adherence, and acceptability outcomes will be collected throughout the trial. To address aim 2, changes in injury-related fear and jump-landing biomechanics will be compared between participants randomized to VRMM+neuromuscular training rehabilitation (NTR) or VR sham+NTR. The study schedule is outlined in Table 1.

**Table 1. T1:** Schedule of events for the trial.

	Screening	Preassessment (wk 1)	Week 1 (3 visits)	Week 2 (3 visits)	Week 3 (3 visits)	Week 4 (3 visits)	Week 5 (3 visits)	Week 6 (3 visits)	Week 7 (3 visits)	Week 8 (3 visits)	Postassessment (wk 8)
Review eligibility	✓										
Informed consent		✓									
Demographics		✓									✓
Clinical history		✓									
Height and weight		✓									✓
Knee-related questionnaires IKDC^a^ Tegner ACL-RSI^b^		✓									✓
Injury-related fear (TSK-11)^c^	✓	✓									✓
Jump-landing biomechanics (LESS-RT)^d^	✓										
Jump-landing biomechanics (motion capture)		✓									✓
Adherence log			✓	✓	✓	✓	✓	✓	✓	✓	
Acceptability survey											✓
Randomization		✓									
Control and experimental intervention (neuromuscular training and virtual reality)			✓	✓	✓	✓	✓	✓	✓	✓	
Adverse event reporting		✓	✓	✓	✓	✓	✓	✓	✓	✓	✓

a IKDC: International Knee Documentation Committee.

b ACL-RSI: anterior cruciate ligament–return to sport after injury scale.

c TSK-11: 11-Item Tampa Scale of Kinesiophobia.

d LESS-RT: Landing Error Scoring System-Real Time.

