### Sample Size Estimation and Study Population

For early-stage pilot and feasibility studies, it has been suggested to include at least 12 participants per group [34]. To achieve aim 1, a minimum of 12 participants in each group will be enrolled (ie, 24 participants). However, we also completed an *a priori power* calculation that determined a sample size of 20 participants per group (40 participants in total), which was required to achieve 80% power to detect a large between-group effect in injury-related fear. This calculation was based on a repeated measures ANOVA with a common SD of 1, a 2-sided α level of 0.05, and an estimated partial η^2^ of 0.23 [35] (moderate effect size) between the intervention and sham groups in injury-related fear. Therefore, a total of 48 participants (24 in each group) will be recruited to account for a 20% dropout rate in the sample and will be appropriate for making interpretations for aims 1 and 2.

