### Limitations and Anticipated Problems

This trial is designed to assess the feasibility and preliminary efficacy of VRMM in patients after ACLR. Therefore, we will not be able to draw any firm conclusions regarding the effectiveness of the VRMM intervention to improve the measured outcomes in this population. A larger randomized clinical trial will be needed to investigate the efficacy of VRMM+NTR compared to VR sham+NTR. The results from this trial will determine whether such a study is feasible and how a fully powered clinical trial may be optimally designed for this purpose.

Additionally, there are a total of 26 participant visits from preassessment to postassessment involved in this trial. Therefore, it is possible that participants may drop out, miss a study visit/visits, or that there may be missing data, which would introduce a risk of attrition bias. The feasibility outcomes are being used to understand these factors, and our sample size was calculated to account for possible attrition. Finally, the TSK-11 scale will be interpreted cautiously in view of the limitation that the scale was not developed specifically for acute musculoskeletal injuries; however, psychometric properties suggest that this scale can be applied to help understand outcomes after ACLR [42].

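### The TSK-11 schedule in the text does not match Table 1, and the 2×2 ANOVA is a valid but inefficient test that subtracts baseline instead of adjusting for it

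*Protocol article*

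**What the plan says.** **Schedule.** The section Injury-Related Fear (Aim 2a) has consented participants complete the TSK-11 at the preassessment, then at "weeks 2, 4, and 6 of the intervention/sham, and the postassessment (wk 8) (Table 1". In Table 1 (Study Design), the row "Injury-related fear (TSK-11)^c" has ticks at screening, preassessment and postassessment only. Its cells for weeks 1 to 8 are empty.

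**Analysis.** The Statistical Analysis section fixes one model for TSK-11, peak knee abduction moment and knee flexion excursion: "A 2×2 repeated measures ANOVA will be used to assess changes between the intervention and sham groups". The effect of interest is the interaction: "Partial η^2^ effect sizes will be calculated to examine the magnitude of the Group × Time interaction". No baseline covariate is named. The test level is set there too: "The significance level will be set at a corrected value of *P*<.02 to reflect multiple comparisons (0.05/3".

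**Attrition.** Limitations and Anticipated Problems accepts that dropout and missing data may occur, "which would introduce a risk of attrition bias". It answers with the feasibility outcomes and a sample size that allows for dropout. Rationale and Principal Findings gives partial η² of at least 0.09 as an example of the efficacy signal that would support a larger trial.

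**The concern.** The text cites a table that disagrees with it about when the main patient-reported outcome is measured. Twelve participants were randomised and ten had completed at the time of writing, so one of the two descriptions already fails to match what was done.

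Whichever is right, the named model has two time levels. If interim TSK-11 scores exist, the main test ignores them. If they do not, the pre-post contrast still makes weaker use of the preassessment value than it could. In a trial of 48 that loss is worth avoiding: the estimate feeds the decision on a larger trial, and adjusting for a baseline already collected costs nothing in data.

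**Working it through.** **1. Schedule, side by side.**
- Text: preassessment, weeks 2, 4 and 6, postassessment (five occasions after consent).
- Table 1: preassessment and postassessment (two occasions after consent), plus screening.
- Table 1 does have columns for weeks 2, 4 and 6, and its adherence row is ticked in every one of weeks 1 to 8. The empty TSK-11 cells are therefore unlikely to be a text-extraction fault.

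**2. What the 2×2 test is.** With two groups and two times, the Group × Time F statistic equals the squared two-sample t statistic on post minus pre. It needs both values from each person and cannot take in a third time point.

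**3. The plan's own sample size.** Inputs from Sample Size Estimation: "repeated measures ANOVA with a common SD of 1, a 2-sided α level of 0.05", "an estimated partial η^2^ of 0.23 [35] (moderate effect size", 80% power, 40 participants before dropout.
- f² = 0.23/0.77 = 0.299; noncentrality λ = N × f²; df 1 and N − 2.
- At α = 0.05 this gives N = 30, with power 0.92 at N = 40. The figure of 40 does come back if α = 0.05/3. That mismatch is a separate matter and nothing below depends on it.

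**4. Change score against ANCOVA.** Let σ² be the common pre and post variance and r the pre-post correlation. The article gives no r, so a range is assumed.
- Variance per person of the change score: 2σ²(1 − r).
- Residual variance after adjustment: σ²(1 − r²).
- Ratio: (1 − r²)/[2(1 − r)] = (1 + r)/2.

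Power uses α = 0.02 and 38 completers (48 × 0.8 = 38.4), taking 0.23 as the interaction partial η². For ANCOVA, λ is divided by the ratio and the error df is N − 3. For the 2×2 ANOVA the power is 0.82, and 38 participants are needed for 80%.

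| r | Variance ratio | Extra participants needed by change score | ANCOVA power | ANCOVA N for 80% |
|---|---|---|---|---|
| 0.3 | 0.65 | 1/0.65 − 1 = 54% | 0.95 | 26 |
| 0.5 | 0.75 | 1/0.75 − 1 = 33% | 0.92 | 30 |
| 0.7 | 0.85 | 1/0.85 − 1 = 18% | 0.88 | 32 |
| 0.8 | 0.90 | 1/0.90 − 1 = 11% | 0.86 | 34 |

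The ratio leaves out the small cost of estimating the slope, on average a factor of about 1 + 1/(N − 4), or 1 + 1/34 = 1.03 at 38 completers.

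**5. What interim scores would add.** The comparison is a baseline-adjusted longitudinal model on five TSK-11 visits against ANCOVA in completers. Dropout is 20%, spread evenly and completely at random; r is 0.3 to 0.7, with compound-symmetric or first-order autoregressive correlation. Variance falls by a further 1% to 7%. Most of the gain therefore comes from step 4.

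**6. Effect on partial η².** If the 2×2 partial η² is 0.09, the adjusted one for the same effect is about 0.09/(0.09 + 0.91 × ratio):
- r = 0.3: 0.09/0.6815 = 0.13
- r = 0.5: 0.09/0.7725 = 0.12
- r = 0.7: 0.09/0.8635 = 0.10
- r = 0.8: 0.09/0.9090 = 0.10

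The two are not interchangeable against a fixed threshold.

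**The case against.** The best defence is that a Group × Time test is an unbiased comparison of change in a randomised trial, and that a less efficient method is not an error. On the reading in step 3 it still has 0.82 power at 38 completers and α = 0.02. The trial's first aim is feasibility, and the article disclaims firm conclusions on effect. All of that stands, and it limits this point to an improvement.

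A reader might go further and infer that the plan throws away every dropout, about 10 of 48, although their interim scores are in hand, and so builds in bias. The documents do not support this:
- The article states no analysis population or missing-data rule, and it may properly leave these to an analysis plan that is not shown. Omission of people without a post score follows from how the method is usually run, not from a stated rule.
- The 20% is a planning allowance, not a count of missing week 8 scores. Someone who stops the sessions but attends the postassessment would be kept.
- Interim scores exist only if the text, not Table 1, describes practice, and only for people who reached week 2.
- No bias has been quantified. Under completely random dropout the completers' contrast is unbiased.

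Nor does ANCOVA cure attrition: it too needs a post value, and the two biomechanical outcomes have no interim measurements to draw on.

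**Conclusion.** Two modest points hold. First, the text and Table 1 contradict each other on the TSK-11 at weeks 2, 4 and 6. The documents do not show which is right.

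Second, the planned analysis is valid but gives up precision. Baseline adjustment would cut the variance of the between-group contrast by 10% to 35% for r from 0.8 to 0.3. This rests on an assumed r, equal pre and post variances, and neglect of the roughly 3% cost of estimating the slope. Interim TSK-11 scores, if collected, would add about 1% to 7% under completely random dropout. Their main value is that people who leave after an interim score still contribute, under the weaker assumption that data are missing at random.

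This is a schedule reconciliation and an efficiency improvement, not a must-fix error.

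**What to change.** - **Reconcile the schedule.** Establish what has actually been collected from those already randomised, then bring the Injury-Related Fear section and Table 1 into agreement with it.
- **Adjust for baseline.** Make the main between-group analysis of all three outcomes an ANCOVA of the post value on the preassessment value, reporting the adjusted mean difference with its 95% CI.
- **If the interim TSK-11 scores are collected,** analyse that outcome instead with a baseline-adjusted mixed model for repeated measures in all randomised participants, with the week 8 group contrast as the test.
- **Protect the progression example.** Partial η² from an adjusted model tends to be larger for the same effect. Either keep the 2×2 ANOVA partial η² as a secondary report for the 0.09 example, or restate that threshold on the adjusted scale.

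The analysis changes cost a paragraph of wording and should be fixed before any unblinded analysis. If the interim scores were not collected from earlier participants they cannot be recovered; the ANCOVA does not need them.

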**Methods:**

A double-blinded, 2-arm feasibility trial of 48 participants (24 per group) comparing VRMM+NTR and VR sham+NTR will be conducted. Recruitment, retention, adherence, and acceptability outcomes will be collected throughout the trial. Injury-related fear will be measured using the 11-Item Tampa Scale of Kinesiophobia. Jump-landing biomechanics will be assessed via peak knee abduction moment and peak knee flexion excursion. The change in outcomes will be compared between groups using 2×2 repeated measures ANOVA and partial η^2^ effect sizes. Significance will be set at *P*<.05.

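### The Abstract tests at P<.05 and the Methods at P<.02 for the same three outcomes, and .02 is not the 0.05/3 it is said to be

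*Protocol article*

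**What the plan says.** Three places in the protocol article bear on the level.

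- **Abstract, Methods.** After naming the 2×2 repeated measures ANOVA, it states: "Significance will be set at *P*<.05". No correction is mentioned.
- **Statistical Analysis.** For the same ANOVA, the level is "set at a corrected value of *P*<.02 to reflect multiple comparisons (0.05/3"). The family has three members: "The TSK-11 score, peak knee abduction moment, and knee flexion excursion will serve as our dependent variables". No hierarchy is given: "Hypotheses for each outcome will be tested independently".
- **Sample Size Estimation and Study Population.** The calculation, for injury-related fear, assumes "a 2-sided α level of 0.05, and an estimated partial η^2^ of 0.23", and arrives at "a sample size of 20 participants per group (40 participants in total), which was required to achieve 80% power". Recruitment is then raised to 48 for dropout.

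**The concern.** A significance level is a decision rule, so it has to be one number. Here the Abstract and the Methods print different cutoffs for the same tests, and the Methods cutoff does not equal the formula beside it. One result could be reported as significant or not depending on which section is followed, and choosing between them after the data are seen would look like choosing the threshold to suit the result. A correction for three outcomes is also meant to hold the chance of any false positive at 5%, and neither printed cutoff guarantees that. Finally, the power figure was worked out at a level that the analysis section does not use for injury-related fear.

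**Working it through.** **Inputs.** Three outcomes, tested separately; cutoffs of .05 (Abstract) and .02, derived as 0.05/3 (Statistical Analysis); two-sided α of 0.05, partial η² of 0.23, 20 per group and 80% power (Sample Size Estimation). The correlation between outcomes is not given.

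**1. The corrected level.** 0.05/3 = 0.01667. The Šidák alternative is 1 − 0.95^(1/3) = 0.01695. Neither is .02, which is 0.01667 rounded up to two decimals.

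**2. Familywise error over three tests.** The bound is 3α, which holds whatever the correlation. With independent tests it is 1 − (1 − α)³.

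| Level per test | Bound | Independent |
|---|---|---|
| .05 | 3 × 0.05 = 15% | 1 − 0.95³ = 14.3% |
| .02 | 3 × 0.02 = 6.0% | 1 − 0.98³ = 5.9% |
| 0.05/3 | 5.0% | 4.9% |

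A simulation of three equally correlated two-sided z tests shows how far correlation lowers these figures. At .02 the error is 5.7% for a correlation of 0.3, 5.3% for 0.5, 4.98% for 0.6 and 4.2% for 0.8. At .05 it is still 8.4% for a correlation of 0.9.

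**3. Which results are affected.** With 40 completers the interaction test has 1 and 38 degrees of freedom, and partial η² = F/(F + 38).

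- P = .05: F = 4.10, partial η² = 4.10/42.10 = 0.097.
- P = .02: F = 5.90, partial η² = 5.90/43.90 = 0.134.
- P = .0167: F = 6.27, partial η² = 6.27/44.27 = 0.142.

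An observed partial η² from 0.097 to 0.134 is significant by the Abstract only. One from 0.134 to 0.142 passes .02 but fails 0.05/3. Both ranges lie within the protocol's own medium band (0.09 to 0.24).

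**4. Power at each level, 40 completers.** The document does not show how 0.23 entered the calculation, so three readings are given.

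- *Partial η² taken literally.* f² = 0.23/0.77 = 0.299. The noncentrality is f² × 40 = 11.9, or f² × 38 = 11.4, depending on the convention.
- *0.23 entered as Cohen's f.* This needs a pre-post correlation, assumed here to be 0.5. The noncentrality is 0.23² × 40 × 2/(1 − 0.5) = 8.46.
- *Back-solved.* Assume that 20 per group gives exactly 80% at 0.05 in a two-group comparison. The noncentral t then gives d = 0.909, which is partial η² of about 0.17, not 0.23.

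| Reading | α = .05 | α = .02 | α = 0.0167 |
|---|---|---|---|
| Partial η² = 0.23, literal | 91-92% | 82-84% | 80-82% |
| f = 0.23, correlation 0.5 (assumed) | 81% | 68% | 66% |
| Back-solved to 80% at .05 | 80% | 67% | 64.5% |

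The literal reading does not reproduce the stated 80% at 0.05 with 40 participants. It gives more. The second reading comes close to the stated figure, but rests on an assumed correlation.

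**The case against.** The strongest reply is that this is editorial. The analysis section is the specific, reasoned statement and the Abstract is a summary. The formula is printed next to .02, so a reader can see two-decimal rounding and recover the intended level. P values, F values and 95% confidence intervals will be reported, so anyone can apply either threshold. The trial is at stage 1 with feasibility as its main purpose, its Limitations section disclaims firm conclusions on effectiveness, and its example criterion for going forward on aim 2 is a partial η² of at least 0.09, not a P value.

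Most of that stands, and it limits the consequence. It does not remove the contradiction: the Abstract does not merely omit the correction but states a different rule.

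Three stronger readings might be inferred, and the document does not support them.

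- *That familywise error exceeds 5% under the .02 rule.* It may, up to 6.0%, but it falls to 5% or below if the outcomes correlate at about 0.6 or more, and no correlation is given. What can be said is that control is not guaranteed.
- *That three competing levels apply to the same tests.* Two cutoffs and one formula are printed. The 0.05 in the sample-size section is a planning input for injury-related fear, not a further decision rule for all three outcomes.
- *That power falls to 67% or 64.5%.* Those figures rest on a back-solved d of 0.909. With the stated partial η² taken literally, 40 completers keep about 80-82% at 0.0167. A loss of the stated power is not shown.

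**Conclusion.** The point holds as an inconsistency in a decision threshold. The .05 against .02 conflict is the larger part: it changes the verdict on any P value between those limits, and the Abstract's rule allows a familywise error of up to 15% (14.3% if the tests are independent). The rounding of 0.0167 to .02 is the smaller part: it affects only P values from .0167 to .02 and adds at most one percentage point to the bound. The power statement belongs to a level other than the one the analysis applies to injury-related fear. Its value at 0.0167 runs from about 65% to about 82% across the readings above, and the document does not settle which applies. I would rate this as something that should be fixed rather than must be, because efficacy is preliminary here and the example go-forward criterion for aim 2 is an effect size.

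**What to change.** State one level throughout. In both the Abstract and Statistical Analysis, write P<.0167 and keep 0.05/3 beside it as the definition. A Holm step-down at familywise 0.05 across the three outcomes is an acceptable option, but no error requires it. In Sample Size Estimation, restate the power at the corrected level and say how 0.23 was entered: as partial η² or as Cohen's f, and with what pre-post correlation if one was used. If 40 completers then give less than 80%, report that figure as it is.

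The cost is wording in three places, and a cutoff slightly stricter than .02. No data collection changes. With 12 participants randomized at the time of writing and completion expected in May 2027, the level can still be settled well before the final analysis.

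### The fixed corrected level for the three aim 2 outcomes is written as .02 where 0.05/3 is .0167; Holm's step-down would keep the 5% level and give more power per outcome

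*Protocol article*

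**What the plan says.** The Statistical Analysis section names three dependent variables (TSK-11 score, peak knee abduction moment, knee flexion excursion), each analysed with a 2×2 repeated measures ANOVA. The significance level is a single corrected value, P below .02, set "to reflect multiple comparisons (0.05/3"). Each outcome's hypothesis is to be tested independently of the others. The expectation covers all three: "We hypothesize that patients in the VRMM+NTR group will demonstrate lower injury-related fear, decreased external knee abduction moment, and increased knee flexion excursion".

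Two other places give a different level. The abstract's Methods paragraph says "Significance will be set at *P*<.05", with no correction. The Sample Size Estimation section uses "a 2-sided α level of 0.05". That section's power statement concerns fear only: 20 per group is described as "required to achieve 80% power to detect a large between-group effect in injury-related fear", based on "an estimated partial η^2^ of 0.23". No effect size is given for either biomechanical outcome, and no correlation among the three.

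The Discussion makes progression to a larger trial depend on the feasibility results and on promising preliminary efficacy, with partial eta-squared of at least 0.09 as the example.

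**The concern.** There are two linked problems.

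1. The written cut-off is not the one its own derivation gives. Rounding .0167 up to .02 loosens the correction, so the familywise error it was meant to hold at 5% is exceeded. A smallest P value between .0167 and .02 would be declared significant by the written number but not by the stated division.
2. A fixed split applies the strictest level to every outcome, whatever the others show. Holm's procedure compares the ordered P values with 0.05/3, 0.05/2 and 0.05 and stops at the first failure. It gives the same familywise guarantee as an exact 0.05/3 split and can only reject the same outcomes or more.

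The three per-outcome conclusions are at stake, above all those for the two biomechanical outcomes. These have no power statement, and about 40 completers are planned.

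**Working it through.** **Inputs.** From the article: three tests; 0.05/3, written as .02; partial eta-squared 0.23 for fear; 20 per group (40 in total) planned to complete out of 48 recruited; Group × Time interaction on two time points, which is a two-sample comparison of change scores with F on (1, 38) degrees of freedom. Assumed, because the article does not give them: partial eta-squared on each biomechanical outcome of 0, 0.09 (the Discussion's own example), 0.14 or 0.23, and a common correlation of 0 to 0.5 among the outcomes.

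**Step 1: the plan's own sample size.** Noncentrality λ = N·η²/(1−η²) = 40 × 0.23/0.77 = 11.95. Power on fear with 40 analysed:
- at alpha 0.05 (the level stated in the sample size section): 92.0%, and about 30 in total would already give 82%;
- at .02: 84.3%;
- at 0.05/3: 82.4%.

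So 20 per group does not follow from the stated alpha, but it is consistent with 0.05/3. It would also follow if 0.23 had been entered as Cohen's f with a pre-post correlation of 0.5 (80.9%), so the article does not settle how the figure arose. In either case, fear keeps at least 80% power under an exact split.

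**Step 2: familywise error, three independent true nulls.**
- At .02: 1 − 0.98³ = 5.88% (simulation 5.8%).
- At 0.05/3: 1 − (1 − 0.05/3)³ = 4.92%.
- Holm: 4.8% by simulation.

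**Step 3: why Holm contains the exact split.** If an outcome has P ≤ 0.05/3, every smaller P also meets 0.05/3. Since 0.05/3 ≤ 0.05/2 ≤ 0.05, all of these pass their Holm steps. Anything rejected at 0.05/3 is therefore rejected by Holm. With m₀ true nulls, the first true null to be rejected faces a threshold of at most 0.05/m₀, so by the union bound the familywise error is at most 0.05 whatever the correlation.

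**Step 4: power per biomechanical outcome.** Fear at 0.23, 20 per group. The fixed-level columns come from the noncentral F and do not depend on correlation. The noncentralities are 40 × 0.09/0.91 = 3.96, 40 × 0.14/0.86 = 6.51 and 11.95. The Holm column comes from 200,000 simulated trials per scenario, with t tests on change scores and d = 2√(η²/(1−η²)).

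| Biomechanical η² | Fixed 0.05/3 | Written .02 | Holm (r = 0 to 0.5) |
|---|---|---|---|
| 0.09 | 0.32 | 0.34 | 0.41 |
| 0.14 | 0.52 | 0.55 | 0.63-0.64 |
| 0.23 | 0.82 | 0.84 | 0.89-0.91 |

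**Step 5: the unfavourable case.** With an effect on fear only, power on fear is 82.3% at 0.05/3, 82.5% under Holm and 84.2% at the written .02. Holm gains almost nothing over the exact split. It loses slightly to .02, but only because .02 spends more than 5%.

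**The case against.** A Bonferroni split is a valid, prespecified way to control familywise error, and choosing it is not a mistake. Fear, the only powered outcome, still has about 82% power at 0.05/3. No power is promised for the biomechanical outcomes, whose true effects may be small: with eta-squared 0.03 on each and independence, power there moves only from 9% to 12.5%. Progression uses effect size, and the Limitations section disclaims firm conclusions. All of this stands and limits the weight of the point. It does not remove the .02 error. Nor does it give a reason to prefer the split, because P values are still prespecified and used to judge each hypothesis.

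Stronger readings are tempting, but the article does not support them.

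- **Loss on the full hypothesis.** Since benefit is predicted on all three outcomes, a reader might infer that the fixed split cuts the chance of supporting the whole aim 2 hypothesis from 77% to 56%. That pair reproduces only with 0.23 on all three outcomes, 40 completers and zero correlation. With correlation 0.5 it is 81% against 64%. With all 48 completing (correlation 0) it is 88% against 73%. With per-outcome power set to 80% at alpha 0.05 (eta-squared 0.171, correlation 0) it is 49% against 27%. More basically, no rule requires all three to be significant. If one did, each test could run at 0.05 with no adjustment (78% in the first scenario), and Holm would not be the remedy.
- **No cost at all.** A reader might infer that Holm is free against the plan as written. That is exact only against 0.05/3. A smallest P between .0167 and .02 passes the written rule and fails Holm's first step. Holm also lacks simple matching confidence intervals.
- **A ceiling of 40.** Forty is the planned number of completers after dropout from 48, not a maximum.

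**Conclusion.** The point holds in a limited form. The written level of .02 contradicts its own derivation and allows about 5.9% familywise error under independence. The abstract's .05 contradicts both. Replacing the fixed level with Holm restores 5% under any correlation. Against an exact 0.05/3 split it adds about 7 to 12 points of power per biomechanical outcome if their partial eta-squared lies between 0.09 and 0.23. That range is an assumption, as are the correlations of 0 to 0.5 and exactly 20 completers per group. Against the written .02 the gain over the same range is about 5 to 9 points. If the biomechanical effects are absent the gain is negligible. The benefit lies in the per-outcome conclusions. The go/no-go decision does not change.

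**What to change.** In the Statistical Analysis section, replace the fixed corrected level with Holm's step-down at familywise 0.05 over the three Group × Time tests: ordered P values against 0.05/3, 0.05/2 and 0.05, stopping at the first failure. Delete .02 and report Holm-adjusted P values (smallest × 3, middle × 2, largest × 1, each no lower than the one before it and capped at 1), to be read against 0.05. Change the abstract's significance sentence to match, and state which level the sample size calculation used.

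The cost is a sentence or two in each place. It needs no extra participants and no new data. The one real drawback concerns intervals: keep the planned 95% confidence intervals and label them unadjusted, or add Bonferroni-level intervals (1 − 0.05/3 = 98.3%) as a conservative companion. If the team prefers to keep the simple split, the minimum correction is to write .0167 and to reconcile the abstract with it.
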